### Subgroup analyses{20b}

At this moment, subgroup analyses have not been taken into account. The variables employed in the minimization algorithm will be subjected to subgroup analyses, but only for the main result, if necessary.

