#### Inclusion and exclusion criteria

The inclusion criteria are patients undergoing aortic revascularization under deep hypothermic arrest circulation in an elective or emergency setting, and patients and families provided informed consent. The exclusion criteria are a history of previous cardiac surgery, preoperative hemoglobin < 90 gL, hematocrit < 30%, platelets < 100 × 10^9^L, and cardiac insufficiency, left ventricular ejection fraction < 50%, patients who died following surgery for a variety of reasons (hemorrhagic shock, heart failure, infection, etc.), or severe aortic stenosis. The discharge criteria are good recovery of cardiac function, hemodynamic stability maintained, and blood counts and other biochemical parameters are normalized.

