#### Double-blind randomization and allocation concealment

Enrolled patients undergoing aortic surgery will be divided randomly into a control group (ANH) and an aPRP group using a computer-generated sequence. Groups will be chosen before patient admission, and all patients and staff will be oblivious to their group assignment. The anesthesiologist will not be informed of the patient assignments, which are recorded and sealed in sequentially numbered opaque envelopes. Nurse anesthetists can give sealed envelopes and tell to prepare the items for the experiment based on group allocations; there are no differences in the look of the two sets of envelopes. The group assignment will be withheld from all patients and anesthesiologists. Following anesthesia induction, the anesthesiologist may perform the various surgeries in accordance with the coded number. Another anesthesiologist will document intraoperative data and followed up on the patient’s discharge. Finally, the data will be analyzed by a professional statistician.

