### Data collection and management

Dedicated staff will record all data and complete a case report form for each patient. Relevant demographic characteristics and the patients’ past medical histories, including age, height, weight, and diagnosis, will be collected at the time of patient inclusion. Intraoperative data, including mean arterial pressure, heart rate, oxygen saturation, and central venous pressure, will be recorded before the beginning and after the end of collection and before and after the return infusion. TEG testing will also be performed before and after the collection and before and after the return infusion. The decision to use blood products such as fibrinogen, prothrombin complex, coagulation factors, and platelets will be made based on the TEG results.

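### The subgroup rule rests on a minimization algorithm that the described allocation does not contain, and it cannot be followed as written; separately, adjusting 24 h drainage for weight and urgency would gain precision

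*Protocol article*

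**What the plan says.** All references are to the protocol article.

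- **Subgroup analyses {20b}**, first sentence: "At this moment, subgroup analyses have not been taken into account". Second sentence: "The variables employed in the minimization algorithm will be subjected to subgroup analyses, but only for the main result, if necessary". No variable is named.
- **Double-blind randomization and allocation concealment**: patients "will be divided randomly into a control group (ANH) and an aPRP group using a computer-generated sequence". It adds: "Groups will be chosen before patient admission". Assignments are "recorded and sealed in sequentially numbered opaque envelopes". The section *Enrolling {16c}* likewise has a computer assign the sequence to groups A and B.
- **Inclusion and exclusion criteria**: patients are eligible "in an elective or emergency setting".
- **Data collection and management**: baseline data "including age, height, weight, and diagnosis, will be collected at the time of patient inclusion". Elective/emergency status is not in that list.
- **Statistical analysis**: continuous variables are compared by independent t-test or Mann–Whitney U test. Repeated measures ANCOVA is mentioned tentatively, in the sentence about departures from normality, with no covariate named.

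**The concern.** Minimization assigns each new patient by looking at the factors of those already enrolled. It needs a declared list of factors and cannot be written out and sealed before patients arrive. A subgroup rule that borrows its variables from minimization therefore has nothing to refer to in this article. Because the analysis is also conditional on being found necessary, the analyst could choose which subgroups to examine, or whether to examine any, after seeing the results. Any subgroup finding would then be post hoc while appearing to be planned.

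A smaller question follows. The minimization reference is the only text that hints at balance on prognostic factors. The trial mixes elective and emergency surgery, and blood collection is scaled to body weight while drainage is measured in mL. Neither factor is named for stratification or adjustment, so precision may be left unused.

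**Working it through.** **1. Allocation and subgroup text side by side**

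| Feature | Allocation sections | What minimization requires |
|---|---|---|
| Source of assignment | computer-generated sequence | computed per patient from factors of those enrolled |
| Timing | before admission | at enrolment, once factors are known |
| Carrier | sealed, numbered envelopes | cannot be sealed in advance |
| Factors | none named | must be listed |

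The descriptions are incompatible. Within the subgroup section, the first sentence (not considered) and the second (will be done, if necessary) also conflict. The phrase about the main result adds a further ambiguity: the Abstract makes drainage at 24, 48 and 72 h primary, while *Study design {8}* gives the main objectives as volumes of allogeneic blood and blood products.

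**2. Inputs for the arithmetic**

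From *Determination of sample size*: 316 ± 102 mL and 378 ± 133 mL at 24 h, 80 per group, 80% power, 5% type I error (two-sided assumed).

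- Difference: 378 − 316 = 62 mL.
- Common SD: √((102² + 133²)/2) = 118.5 mL.
- Standardized difference: 62/118.5 = 0.523.

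**3. The plan's own figure**

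n per group = 2(1.960 + 0.842)²/0.523² ≈ 57.4, so 58 (59 with the t distribution). The stated 80 is not reproduced; at 80 per group power is about 91%. That is a separate matter and nothing below depends on it.

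**4. Power of one exploratory interaction**

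Let q be the share of patients in the smaller subgroup (assumed; the article gives none). The SE of the interaction is 118.5 × √(2/(80q) + 2/(80(1 − q))), and power for a 62 mL interaction is Φ(62/SE − 1.96).

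| q | SE (mL) | Power |
|---|---|---|
| 0.5 | 37.5 | 38% |
| 0.3 | 40.9 | 33% |
| 0.2 | 46.8 | 26% |

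**5. Gain from covariates**

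The unadjusted SE of the 24 h difference is 118.5 × √(2/80) = 18.7 mL. With covariates explaining a share R² of the variance (assumed), it is multiplied by √(1 − R²), and the equivalent sample-size factor is 1/(1 − R²).

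| R² | SE (mL) | Reduction in SE | Sample-size factor |
|---|---|---|---|
| 0.10 | 17.8 | 5% | 1.11 |
| 0.20 | 16.8 | 11% | 1.25 |
| 0.30 | 15.7 | 16% | 1.43 |

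Residual degrees of freedom fall from 158 to 156.

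**6. Scale of chance imbalance**

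Under simple randomisation with an assumed 30–50% emergencies, the SD of the between-arm difference in emergency share is √(2f(1 − f)/80): 7.2 points at f = 0.3 and 7.9 at f = 0.5. The 95% range is about ±14 to ±15.5 points. If emergencies drained 100 mL more (assumed), a 15-point imbalance would move the estimate by 0.15 × 100 = 15 mL, below one unadjusted standard error (18.7 mL).

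**The case against.** A reader might infer that leaving out urgency and weight biases the primary comparison. The documents do not support that. An unadjusted comparison of randomised arms is valid, and chance imbalance is already part of its standard error and type I error. The 15 mL illustration combines an extreme imbalance with an assumed 100 mL gap, close to a full SD on the article's own figures, and still stays within one standard error. Nor do weight-based collection and drainage in mL contradict each other, since both arms are dosed per kg.

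It can also be said that the article does not commit to an unadjusted model, because it mentions ANCOVA. That is correct, but the mention is tentative, tied to non-normality and names no covariates, so it fixes nothing. Covariate choice is commonly left to an analysis plan or full protocol not shown here, so its absence is not an error. On the stated inputs power at 80 per group is already about 91%, so the precision gain does not rescue an underpowered trial.

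Finally, minimization may really have been used, with factors that the article does not name. The documents cannot exclude this. In that case the allocation sections would be wrong, and tests that ignore the factors would generally overstate the standard error when those factors are prognostic. The inconsistency needs correcting on either reading.

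**Conclusion.** The inconsistency is established from the text alone and needs no assumption: the subgroup rule conflicts with the allocation sections and with the sentence before it, and it cannot be carried out as written. It affects the standing of any subgroup result, not the validity of the randomised primary comparison.

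The covariate point is a recommendation for precision, not the correction of a bias. Its size, a 5–16% smaller standard error, rests on an assumed R² of 10–30%, for which the article gives no data. The power range for an interaction rests on assumed subgroup shares.

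**What to change.** 1. Delete the minimization reference. Then either state that no subgroup analysis is planned, or name the elective/emergency by treatment interaction as the single one, for 24 h drainage, labelled exploratory and with its low power acknowledged.
2. If minimization was in fact used, correct *Enrolling {16c}* and the allocation section, list the factors, and adjust the primary analysis for them.
3. As an improvement, prespecify a primary model for 24 h drainage with treatment, body weight and elective/emergency status. Weight is collected at inclusion. Urgency is known at enrolment but should be added to the case report form, since the listed baseline items do not include it.

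The cost is wording, one case report form item and two degrees of freedom, with no extra patients. *Unblinding {17b}* places the first unblinding step after database lock, and the changes should be fixed before that step.

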### The treatment of non-adherence and missing data{20c}

If there is a clear violation of the protocol, the trial should be stopped, and the subject’s data should be blinded and not included in the final statistical results; if it can be adjusted in time and does not make a significant difference, the data set can be retained. If there are missing data cases, replacement of the data can be tried if necessary, based on the dataset’s characteristics and qualities.

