**Methods and analysis:**

This is a prospective, single-center, double-blind controlled clinical trial including 160 patients randomized 1:1 to receive aPRP (test group) or autologous whole blood (ANH, control group). The primary objective is to compare the drainage volumes in the two groups at 24, 48, and 72 h postoperatively. Secondary outcomes include input of allogeneic blood and blood products and durations of aortic block, extracorporeal circulation, deep hypothermic arrest of circulation, tracheal extubation, hospital stay, requirement for secondary surgical hemostasis, and application of intra-aortic balloon pump or extracorporeal membrane oxygenation in the two groups. In addition, heart rate, systolic blood pressure, diastolic blood pressure, central venous pressure, and thromboelastography recorded before blood reservation (T1), after blood reservation (T2), before blood transfusion (T3), and after the blood is returned (T4) to the transfusion will be compared between the two groups of patients.

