## Interventions

### General anesthesia

All patients will receive general anesthesia as follows: induction with midazolam 0.05 mg/kg, etomidate 0.3 mg/kg, sufentanil 0.5 μg/kg, and cis-atracurium 0.2 mg/kg. The anesthesia machine is connected after tracheal intubation, with the tidal volume set at 6–8 mL/kg and the respiratory rate at 12 breaths/min. The intraoperative end-tidal CO_2_ pressure is maintained at 35–45 mmHg by adjusting the respiratory parameters. Anesthesia is maintained with continuous pumping of 4–8 mg/kg/h propofol, with sufentanil and cis-atracurium injections at regular intervals. After induction of anesthesia, a large-diameter catheter is placed in the patient’s right internal jugular vein. The red blood cells were reinfused back into the patient after collection, and the collected aPRP was infused back into the patient after extracorporeal circulation following neutralization of heparin with fisetin.

There is no universally accepted criterion for determining the ideal amount of whole blood to collect for ANH, which is sometimes established clinically by diluting the target hematocrit or blood volume. However, according to the 2019 expert agreement on the clinical treatment of autologous blood transfusion, the total volume for blood collection should be as follows: 10–15% of total blood volume, with an increase to 20–30% of total blood volume in rare instances or in patients with improved health status. Accordingly, autologous blood is taken from the internal jugular vein following anesthesia and central venous cannulation with a volume of 8–10 ml/kg and Hct > 30% before CPB in the ANH group, and acute isovolumic hemodilution with sodium acetate-Ringer solution is conducted. If the collected blood is required for extracorporeal circulation reasons, this test will exclude this case. Ringer’s acetate will be used as a volumetric substitute to maintain hemodynamic stability throughout the blood collection process at a ratio of 1:1.5 (volume replenishment). Previous studies used crystalloids at a ratio of 1:3, and a pre-study test demonstrated that a ratio of 1:1.5 provided safe and effective volume replacement. At the end of the procedure, the patient is returned to the cardiac surgical care unit with assisted ventilation with a respiratory ball.

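### Clear protocol violators are left out of the final results, other deviators are kept on an undefined judgement, and no all-randomised analysis is named

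*Protocol article*

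**What the plan says.** The rule is in the protocol article under *The treatment of non-adherence and missing data {20c}*. It has two parts.

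- Clear violations: the trial is to stop, which I read as applying to that subject's participation, and the rule for that subject is: "data should be blinded and not included in the final statistical results; if it can be adjusted in time". The closing words of this quote already open the second part.
- Other deviations: "if it can be adjusted in time and does not make a significant difference, the data set can be retained". Both conditions apply: timely adjustment and no significant difference.

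Two other sections remove patients because of events that can only occur after enrolment:

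- *Inclusion and exclusion criteria* lists among the exclusions "patients who died following surgery for a variety of reasons (hemorrhagic shock, heart failure, infection, etc".
- *General anesthesia*, in the paragraph on ANH collection, says: "If the collected blood is required for extracorporeal circulation reasons, this test will exclude this case".

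The abstract describes "160 patients randomized 1:1 to receive aPRP (test group) or autologous whole blood (ANH, control group". *Statistical analysis* names the tests but no population, and no section states that patients are analysed as randomised.

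**The concern.** Randomisation makes the two groups comparable only while everyone randomised stays in the comparison. Here, membership of the analysed groups depends on what happens during and after the procedure. Neither a clear violation nor a significant difference is defined, and the article does not say who judges them or whether this happens before the allocation or the outcome is known.

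If the patients removed differ in bleeding from those who stay, and the removal differs by arm, the drainage comparison shifts for reasons unrelated to treatment. Losing high drainers from the aPRP arm would overstate its benefit; losing them from the ANH arm would understate it. The two further exclusions act in the same way. The exclusion of deaths names hemorrhagic shock, which is close to the outcome being measured.

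**Working it through.** **Inputs.** From *Determination of sample size*: 24 h drainage of 316 (SD 102) mL with aPRP and 378 (SD 133) mL in controls; 80 per group; 80% power; 5% type I error (two-sided assumed). Planned difference: 378 − 316 = 62 mL. Pooled SD: √((102² + 133²)/2) = 118.5 mL. The article gives no exclusion rate and no selection pattern; those used below are assumptions.

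**The plan's own figure.** n per group = 2 × (1.96 + 0.84)² × 118.5²/62² gives 58 (59 with the t-test), not 80. With 80 per group, power is 91%. That mismatch is a separate point, and nothing here depends on it.

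**Is the harm lost power?** Power = Φ(62/(118.5 × √(2/n)) − 1.96), with equal losses in both arms:

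| Excluded | n per arm | Power |
|---|---|---|
| 0% | 80 | 91% |
| 10% | 72 | 88% |
| 20% | 64 | 84% |
| 25% | 60 | 82% |

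Power stays above 80% throughout, so the issue is bias.

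**Shift in one arm's mean.** Suppose a fraction f is removed by selection on a normal variable that correlates ρ with drainage. The mean falls by ρ × SD × φ(z)/(1 − f), where z cuts off the top fraction f. For f = 10%, φ(1.2816)/0.9 = 0.1755/0.9 = 0.195.

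| Selection | aPRP arm (SD 102) | ANH arm (SD 133) | Share of 62 mL |
|---|---|---|---|
| ρ = 0.5 | 10.0 mL | 13.0 mL | 16% to 21% |
| ρ = 1 (only the highest drainers) | 19.9 mL | 25.9 mL | 32% to 42% |

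**Both arms losing 10% in the same way.** The shifts largely cancel:

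- ρ = 0.5: 13.0 − 10.0 = 3 mL (about 5% of 62 mL)
- ρ = 1: 25.9 − 19.9 = 6 mL (about 10%)

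**Effect on type I error.** This was simulated with no true effect: 20,000 runs, 80 per arm, SD 118.5 mL, with patients removed from one arm only and drawn at random from its upper half of drainage.

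| Removed from one arm | False difference | Type I error |
|---|---|---|
| 5% (4 patients) | 5 mL | 5.5% |
| 10% (8 patients) | 11 mL | 8.4% |
| 15% (12 patients) | 17 mL | 12.9% |

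**The case against.** **It belongs in the analysis plan.** Definitions of violation classes are often left to a fuller document, and their absence alone would not be a finding. The exclusion itself, however, is stated. A separate plan could restore an as-randomised primary analysis only by contradicting it.

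**Outcome-driven retention.** A reader might infer from "does not make a significant difference, the data set can be retained" that deviators are kept or dropped according to their effect on the trial result. The text allows that reading but does not establish it. The condition stands beside timely adjustment, which suggests a judgement of materiality during conduct, whereas drainage is read at 24 to 72 h. Nor does the clause screen all remaining patients; it covers only those who deviated. The rule is written in advance, so only the case-by-case judgement is made after the event. What stands is that the criterion is undefined.

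**Unequal violations by arm.** A reader might also take it as established that violations will be unbalanced and will track bleeding. The techniques do have different requirements: a separator and a target yield for aPRP, a volume and hematocrit limit for ANH. But the article reports no failure rates, does not class a missed target as a clear violation, and links no deviation to bleeding. Imbalance is plausible, not documented.

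**Blinding.** *Unblinding {17b}* puts database lock before even the A/B-level unblinding. That helps, but the article does not say that exclusions are settled by then. Removal on post-randomisation events can bias the comparison even when whoever decides is blinded.

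**Missing data.** The sentence that "replacement of the data can be tried if necessary" leaves the imputation method open. That is ordinary content for an analysis plan and is not part of this point.

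**Conclusion.** The point holds as a stated rule. The final results omit clear violators, retain other deviators on an undefined judgement, and are not accompanied by an all-randomised analysis. Two further sections add exclusions based on post-randomisation events.

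The actual bias cannot be computed from the document. With an assumed 10% loss, it ranges from about 3 to 6 mL net when both arms lose patients alike, to 10 to 26 mL when only one arm does, against 62 mL planned. The upper end needs the extreme assumption that only the highest drainers of a single arm are lost. The documents support no claim that this will happen, only that the plan does not guard against it. Because the rule determines who enters the primary comparison, it should be changed before analysis.

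**What to change.** 1. State that the primary analysis includes all randomised patients who undergo surgery, in their assigned group, regardless of adherence.
2. State that drainage on postoperative days 1 to 3 is still recorded after a violation. The current instruction to stop leaves this unclear.
3. Delete the clause that makes retention depend on the absence of a significant difference.
4. Keep a per-protocol set as a sensitivity analysis only, with membership defined and fixed before the first (A/B) unblinding.
5. Reconcile the analysis exclusions in *Inclusion and exclusion criteria* (deaths after surgery) and *General anesthesia* (collected blood needed for extracorporeal circulation) with this population. Otherwise the first change alone does not restore the randomised comparison. This concerns who is analysed, not how patients are managed.

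The cost is protocol wording and continued drainage recording for violators. No stated figure changes: with all 80 per arm kept, power is 91% on the article's own inputs. The downside is an estimate possibly diluted by non-adherence, which is why the per-protocol result should be shown beside it.

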### Interim analyses {21b}

Regular meetings are held to evaluate and correct the trial as necessary. However, in this trial, interim analysis is not planned.

### Statistical analysis

Statistical analysis will be carried out using the SPSS software, version 26.0 for Windows (SPSS, Inc., Chicago, IL, USA). Continuous variables will be described as mean (standard deviation) or median (25% and 75% percentiles) and analyzed using independent *t*-tests or Mann–Whitney *U* tests, respectively. Categorical variables will be described as a frequency or percentage and analyzed by *χ*^2^ tests. Prior to statistical analysis, each continuous variable will be analyzed to determine if it is normally distributed. If the assumption of a normal distribution is violated, the appropriate transformation will be used, and analysis using repeated measures analysis of covariance (ANCOVA) models may be more effective.

### Important protocol modifications{25}

If problems are discovered and the trial protocol needs to be modified or adjusted, the reasons, contents, and timing of the modification should be stated, and the application should be submitted to the ethics committee for approval and consent before implementation; if the modification of the trial protocol during the clinical trial involves the informed consent of the subjects, the informed consent form should be changed; or if there is a new modification or addition to the trial protocol, the informed consent form should be changed.

